### 2.6. Intervention

#### 2.6.1. Virtual Reality Plus Standard of Care (Vr + Soc)

Participants allocated to the intervention group undergo PICC or PICC-PORT placement according to institutional standard procedures, combined with the use of an immersive virtual reality system delivered via a head-mounted display during the procedure.

The VR system used is a commercially available Class I non-sterile medical device, compliant with EU Regulation 2017/745 (Medical Device Regulation) [21]. The device delivers immersive audiovisual content, integrating visual environments, guided breathing, and structured audio designed to promote relaxation and attentional engagement. See Supplementary Materials File S1, for further technical information.

The VR device does not record, store or transmit any personal or clinical data, and its use does not involve data processing activities beyond content visualisation. Prior to the procedure, patients may select among different visual and audio environments. Throughout the intervention, verbal interaction with healthcare professionals is continuously maintained, assuring safety and preserving the usual communicative flow of the procedure.

The VR intervention is implemented exclusively as a supportive, non-pharmacological adjunct to standard care and does not replace clinical communication, procedural monitoring or operator–patient interaction during device placement. All standard clinical care procedures are permitted and are not altered by the intervention. In the case of cybersickness or clinically relevant symptoms such as nausea, dizziness or visual discomfort, the operator is ready to assess and intervene, including removing the VR device if necessary. In such cases, the procedure continues according to standard care.

#### 2.6.2. Standard of Care (Soc)

Participants allocated to the control group undergo PICC or PICC-PORT placement according to the same institutional protocols, without the use of VR. All clinical aspects of care, including local anaesthesia, monitoring and procedural management are identical to those applied in the intervention group.

#### 2.6.3. Standardisation and Expectancy Control

To minimise expectancy and placebo effects, a standardised information procedure is applied to both study groups. Information is delivered according to a predefined script and administered by a specifically trained registered nurse who is not involved in outcome assessment.

Participants allocated to the control group receive neutral standard information regarding the timing and phases of the procedure. Participants allocated to the VR group additionally receive a brief (approximately 120 words), neutral description of headset use, including instructions that they will wear the device during the procedure, that they may view different visual scenarios and instructions on how to promptly communicate any discomfort or issues to the clinical staff. This information explicitly excludes any reference to potential benefits or expected effects of VR use.

Operators are instructed not to provide feedback or engage in discussion about the content experienced during or immediately after the intervention in either group, in order to avoid differential attention and expectancy-related bias.

### 2.7. Outcomes

The primary outcome of the study is a composite patient-reported procedural experience endpoint, reflecting the overall effectiveness of the virtual reality intervention during PICC and PICC-PORT placement. Although the term “composite endpoint” is used, it refers here to a conceptual and experiential framework rather than to a statistically aggregated outcome.

This composite endpoint integrates multiple dimensions of procedural experience, including:change in procedural anxiety, which represents the prespecified principal quantitative driver of the endpoint;patient-reported comfort and satisfaction with the procedure;perceived procedural acceptability and overall tolerability.

Procedural experience is assessed immediately after completion of the procedure (T1) using structured patient-reported measures, combining ordinal rating scales and qualitative evaluation to assess complementary quantitative and experiential elements. Procedural anxiety (measured using the 10-point Visual Analogue Scale for Anxiety, VAS-A) constitutes the primary focus of analysis, while the remaining component dimensions (comfort, satisfaction and procedural tolerability) are analysed as individual, non-aggregated measures and interpreted jointly with anxiety to provide an overall understanding of procedural experience. No numerical aggregation of component scores is applied.

This approach reflects the multidimensional and subjective nature of immersive digital interventions, for which patient experience constitutes a clinically meaningful outcome.

Secondary outcomes include:procedural pain, assessed using a 10-point Visual Analogue Scale (VAS);physiological parameters, including heart rate and systolic, diastolic and mean arterial pressure as routinely monitored;procedural characteristics, including procedure duration and number of insertion attempts;qualitative assessment of patients’ perceptions and lived experiences related to the procedure, analysed using Van Kaam’s phenomenological method [18].

This exploratory analysis aims to elucidate the relationship between procedural anxiety and the other experiential dimensions and to facilitate comparison with previous studies in which anxiety was evaluated as a standalone outcome. Procedural pain and anxiety are therefore analysed separately to explore their individual contributions to the overall procedural experience.

### 2.8. Data Collection and Timing

Recruitment strategy

Participants are recruited consecutively from patients scheduled to undergo PICC or PICC-PORT placement at the hospital where the study is conducted. Screening for eligibility, based on the predefined inclusion and exclusion criteria, is performed on the day of the procedure by a member of the study nursing team. Eligible patients are then approached prior to entry into the procedural room or outpatient surgical area, provided with detailed study information and invited to participate. In the case of a positive response, written informed consent is obtained.

Based on institutional activity in 2024, with an average of approximately 15–20 PICC/PICC-PORT insertions per week, a recruitment rate of around 8–10 patients per week can be conservatively anticipated. Accordingly, the target sample size of 120 participants is expected to be reached within approximately 10–12 weeks of active, continuous recruitment. Participant flow through the study will be documented using a CONSORT-compliant flow diagram, anticipated to guide reporting of the main trial results [22].

Data are collected at two predefined time points using a structured case report form specifically developed for the study and subsequently entered into the REDCap electronic database, Figure 1.
T0 (pre-procedural): within 2 min of room entry and prior to preparation of the sterile field, baseline procedural anxiety, pain intensity and physiological parameters (heart rate and arterial blood pressure) are recorded.T1 (post-procedural): within 2 min of completion of the procedure, after removal of the VR headset (for the intervention group) and before the patient leaves the procedural room, patient-reported outcomes related to procedural experience and satisfaction are collected, together with brief qualitative questions exploring patients’ perceptions and experience of the procedure.

Data quality and qualitative rigour

Qualitative data are collected using open-ended prompts administered by a trained research nurse who is not involved in PICC/PICC-PORT insertion or intervention delivery.

The qualitative component follows Van Kaam’s phenomenological method [18] both in data collection and analysis. Methodological rigour is supported through: (a) interviewer training in neutral and non-directive questioning; (b) reflexive documentation by the research team; (c) maintenance of an audit trail; and (d) regular analytic oversight to ensure consistency and transparency of interpretation, in accordance with established qualitative research criteria [23].

As all assessments take place during a single clinical encounter, no specific retention strategies are planned. The only potential source of missing data is interruption of the procedure for clinical reasons (e.g., patient distress or technical failure), which will be documented and reported in the CONSORT flow diagram.

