### 2.5. Randomization and Allocation

Participants are randomly assigned to one of the two study arms in a 1:1 allocation ratio. The randomisation sequence is generated using an independent, certified web-based randomisation service (Sealed Envelope™, London, UK). Simple randomisation is employed [20], without any a priori constraint on final group size, consistent with the pragmatic, real-world nature of the trial.

According to the pragmatic approach of the study, no stratification procedures are applied. Allocation concealment is maintained through centralised, real-time assignment by the online system. After eligibility is confirmed and informed consent obtained, the treating clinician accesses the secure Sealed Envelope web interface, which reveals the allocation at the point of assignment, thereby ensuring concealment at the time of assignment and preventing foreknowledge of upcoming allocations.

Given the characteristics of the intervention, blinding is not feasible at any stage of the study. Participants are aware of whether they are receiving the VR intervention, and healthcare professionals involved in device placement are likewise aware of group allocation.

Blinding of outcome assessment is not feasible for the primary and secondary patient-reported outcomes, which are collected directly from participants aware of their allocation.

All outcomes are collected using standardised instruments applied uniformly across study arms. To mitigate the risk of bias, the operator performing the procedure is not involved in the collection of patient-reported outcomes, and objective parameters (physiological and procedural data) are extracted from clinical records by research personnel not involved in the procedure. The absence of blinding is acknowledged as an inherent methodological limitation and is considered in the interpretation of study findings.

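### The protocol does not fix the T0 anxiety rating before allocation is revealed, so as written the baseline half of the change score may be rated with the arm known

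*Protocol article*

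**What the plan says.** **Consent.** Section 2.8: "Eligible patients are then approached prior to entry into the procedural room or outpatient surgical area", and written consent is taken if they agree.

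**Allocation.** Section 2.5: "After eligibility is confirmed and informed consent obtained, the treating clinician accesses the secure Sealed Envelope web interface". The system shows the arm when it assigns it. Consent and eligibility are the only stated preconditions. No place is given, and no order relative to T0.

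**T0.** Section 2.8 anchors it to the room: "within 2 min of room entry and prior to preparation of the sterile field, baseline procedural anxiety", together with pain, heart rate and blood pressure.

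**Arm-specific steps.** Section 2.6.3: "Participants allocated to the VR group additionally receive a brief (approximately 120 words), neutral description of headset use". Section 2.6.1: "Prior to the procedure, patients may select among different visual and audio environments". Neither is timed relative to T0.

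**Awareness.** Section 2.5: "Participants are aware of whether they are receiving the VR intervention".

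**Analysis.** The Outcomes and Aim section makes the between-group comparison of VAS-A changes the main analysis. Section 2.10 specifies an independent-samples t-test or a non-parametric equivalent, and plans no formal multivariable adjustment.

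**The concern.** T0 and the reveal are tied to different events (room entry and consent), and nothing in the visible text links the two. A team following the protocol to the letter could consent a patient outside the room, open the randomisation page, read the headset script, offer the choice of scene, walk the patient in and only then record baseline anxiety.

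A self-rated anxiety score taken at that point can respond to the news of the allocation: relief, disappointment, or worry about wearing a headset. Such a reaction would differ by arm, because the news differs by arm.

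Two things are at stake. First, T0 is half of the primary quantity, so a distortion in it enters the treatment contrast. Second, Sections 2.10 and 4 treat baseline anxiety as a potential confounder to be used in interpreting the results. With simple, unstratified randomisation, a check of balance on anxiety has some value, and a T0 taken after the reveal could not be relied on for it.

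**Working it through.** **1. Order of events.** The stated constraints are:
- approach for consent before room entry (2.8);
- reveal after consent (2.5);
- T0 within 2 minutes of room entry and before the sterile field (2.8);
- scene choice before the procedure (2.6.1);
- headset script to patients already allocated, so after the reveal (2.6.3).

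At least two sequences satisfy all of them:
- A: consent, reveal, script and scene choice, room entry, T0, sterile field.
- B: consent, room entry, T0, reveal, script and scene choice, sterile field.

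Only B protects the baseline. The visible text does not choose between them.

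**2. How a T0 shift enters the estimate.** Let d be the VR-minus-control shift in mean T0 caused by knowing the arm, and c the fraction of it that persists to T1. The contrast in change, T1 minus T0, is then

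true effect + c·d − d = true effect − (1 − c)·d.

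The bias is zero if the reaction persists in full (c = 1) and −d if it has gone by T1 (c = 0). The sign of d is unknown. Adjusting for T0 with slope b, when T1 is unaffected, leaves a bias of −b·d. With equal SDs, b equals the T0–T1 correlation, so adjustment removes only part of the bias.

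**3. The plan's own figure.** Inputs from Section 2.10: difference 1.5, SD 2.5, two-sided alpha 0.05, power 80%.

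n per group = 2 × (1.960 + 0.842)² × 2.5² / 1.5² = 43.6, rounded up to 44.

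The stated 44 is reproduced. The t-test version gives 44.6, so 45, an immaterial difference.

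**4. Illustration at the target size.** About 120 participants at 1:1 is 60 per arm. The standard error of the contrast is 2.5 × √(2/60) = 0.456. The values of d are assumptions, because the documents give none. Results are from the noncentral t-distribution with c = 0:

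| Shift in T0 | False-positive rate, no true effect | Power for 1.5 if the shift works against VR |
|---|---|---|
| 0 | 5% | 90.3% |
| 0.3 | 10.0% | 74.1% (apparent difference 1.2) |
| 0.5 | 19.2% | 58.4% (apparent difference 1.0) |

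A 0.5-point shift is 0.5/1.5 = 33% of the target difference. If half of it persists to T1 (c = 0.5), the net bias is 0.25 points, and the figures become 8.4% and 77.5%.

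**5. Sensitivity to the SD.** Section 2.10 does not say whether 2.5 is the SD of the change or of a single rating. If it is the SD at each time point, the change SD is 2.5 × √(2(1 − ρ)). That gives 2.96, 2.50 and 1.94 for ρ = 0.3, 0.5 and 0.7. A 0.5-point shift with c = 0 then gives false-positive rates of about 15%, 19% and 29%.

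**The case against.** A reader might infer that allocation is revealed straight after consent, outside the room, so that every baseline is rated with the arm known. The documents do not support that. Section 2.5 sets only an earliest point for the reveal and gives no location. Sections 2.5, 2.6 and 2.8 are arranged by topic, so their order on the page is not a sequence of events. Scene choice before the procedure does not settle the matter either, because T0 is itself labelled pre-procedural. Figure 1, the participant timeline, is not shown and might state the order. All of this stands, and it limits the point to an order that is not fixed.

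Safeguards also exist. The information script is predefined, neutral and silent on benefit, and it is given by a nurse who does not assess outcomes. The protocol openly accepts the risk of expectation bias. These measures make a large shift less likely, but they do not hide the arm.

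The sizes above are assumed, and the error rates are inflated only to the extent that the reaction fades by T1. That also stands. Finally, a late T0 does not remove every check on randomisation: demographic and clinical characteristics cannot be altered by knowing the arm. What is weakened is the check on anxiety itself.

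The objection does not dispose of the point as mere missing detail. The article specifies T0 to within two minutes, but against room entry and not against allocation. An analysis plan cannot fully repair a baseline that was collected after the reveal.

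**Conclusion.** The point holds in this limited form: the protocol permits, but does not require, a baseline rated with the arm known. Because the main analysis is an unadjusted comparison of change in a self-reported score between unblinded arms, a differential T0 shift of d biases the estimate by up to the full d, in an unknown direction.

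The figures of about 19% false positives, or 58% power instead of 90%, are illustrative. They rest on an assumed 0.5-point shift, a change SD of 2.5, 60 per arm and no carry-over to T1. Full carry-over would leave the estimate unbiased. Whether any shift occurs cannot be determined from the documents. The change is still worth making, since it removes the risk at little cost. The sample size is unaffected.

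**What to change.** State in Sections 2.5 and 2.8 that T0 (VAS-A, pain, heart rate, blood pressure) is completed after consent and before the web allocation is revealed, and that the arm-specific script and scene choice follow the reveal. Record the clock time of T0 on the case report form so that it can be checked against the randomisation time. If this is already the practice, one sentence in each section and the time field are enough.

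The cost is a small change in workflow. Either the randomisation page is opened a few minutes later, which puts the reveal, script and scene choice between T0 and the sterile field, or T0 is taken just before room entry, which measures anxiety at a slightly different moment. One time field is added, and no new measurements are needed.

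If T0 cannot be placed before the reveal, a between-arm comparison of T1 scores would avoid relying on a post-allocation baseline. Adjusting for such a T0 would not fully remove the bias.

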### 2.9. Measures

#### 2.9.1. Quantitative Measures

Anxiety and pain are assessed using validated 10-point visual analogue scales, respectively: VAS-A, with scores ranging from 0 (no anxiety) to 10 (worst possible anxiety), and a 10-point VAS for pain.

Physiological parameters, including heart rate and arterial blood pressure, are recorded through standard clinical monitoring devices routinely used during vascular access placement.

Local anaesthetic administration follows institutional protocols. The type and total administered dose of anaesthetic agent are recorded descriptively as part of the data collection.

Patient-reported comfort and procedural tolerability are measured using 5-point Likert scales (1 = very poor to 5 = excellent). Patient satisfaction is assessed using a 10-point Visual Analogue Scale ranging from 0 (not at all satisfied) to 10 (completely satisfied).

#### 2.9.2. Qualitative Component

Qualitative data are collected using open-ended prompts and analysed according to Van Kaam’s phenomenological method [18]. Procedures to ensure qualitative rigour and trustworthiness, including interviewer training, reflexive documentation, audit trail maintenance and analytic oversight, are described in Section 2.8.

See the Supplementary Materials to view the approved dataset, File S2.

### 2.10. Data Management Plan and Analysis

Study data will be entered into an electronic database in REDCap, used exclusively for data management and not for randomisation. All entered data will be pseudonymised, and access will be restricted to personnel specifically authorised for the study through dedicated password-protected accounts. The data will be stored on an institutional server of the study hospital and retained according to the relevant regulations. Identifiable information will be kept separate from research data, ensuring full confidentiality.

De-identified individual participant data, the data dictionary and the statistical code will be made available upon reasonable request to the Principal Investigator. No identifying information will be shared.

Given the minimal-risk nature of the study and its single-centre design, no formal monitoring of trial conduct is planned. The research team will oversee the study, protocol adherence and data collection as part of routine clinical practice.

All analyses will be conducted according to the intention-to-treat (ITT) principle. Descriptive statistics will be used to summarise participants’ demographic and clinical characteristics. Continuous variables will be reported as means and standard deviations or medians and interquartile ranges, as appropriate, according to variable distribution, while categorical variables will be presented as frequencies and percentages.

For the primary composite outcome, between-group comparisons will focus on procedural anxiety (VAS-A) as the prespecified principal quantitative driver of the composite endpoint. Independent samples Student’s *t*-tests, or non-parametric equivalents when appropriate, will be used for between-group analyses. Patient-reported comfort, satisfaction and procedural tolerability will be analysed as individual, non-aggregated component dimensions of the composite endpoint using appropriate parametric or non-parametric methods and interpreted jointly with anxiety. Secondary quantitative outcomes, including procedural pain and physiological parameters, will be analysed using similar inferential methods.

Within-group pre- and post-procedural comparisons will be explored using paired statistical tests. Statistical significance will be set at a two-sided *p* < 0.05.

The planned sample size is based on a power-based rationale focusing on procedural anxiety as the principal quantitative driver of the primary composite outcome. Assuming a clinically relevant between-group difference of approximately 1.5 points on a 10-point VAS-A, a standard deviation of 2.5, a two-sided alpha level of 0.05 and 80% power, a minimum of 44 participants per group is required. To account for uncertainty in effect size estimates, anticipated variability in a real-world clinical context and potential missing data or protocol deviations, the target sample size was increased conservatively to approximately 120 participants, consistent with the trial registration.

Missing data will be handled using complete-case analysis. If the proportion of missing data exceeds 10% for any key variable, sensitivity analyses may be performed to assess the robustness of the results.

No formal multivariable adjustment is planned, in line with the exploratory and pragmatic nature of the trial and the sample size, which is powered for the anxiety-driven component of the primary outcome. Potential confounders (e.g., baseline anxiety, pharmacological therapies and clinical context) are prospectively collected to support informed interpretation of outcome variability rather than formal statistical adjustment.

The study team will perform periodic internal monitoring of data completeness and protocol adherence using REDCap audit trails.

Qualitative data will be analysed using Van Kaam’s phenomenological method [18], involving systematic coding, identification of recurring themes and synthesis of the essential meanings of patients’ lived experiences. Quantitative and qualitative findings will be integrated at the interpretation stage using a narrative approach, whereby qualitative themes are used to contextualise and deepen understanding of the quantitative results. No formal mixed-methods integration techniques (e.g., data transformation or joint displays) are planned, given the protocol focus and exploratory aims of the qualitative component. Statistical analyses will be conducted using dedicated statistical software.

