### Outcomes and Aim

The primary outcome of this study is a composite patient-reported procedural experience endpoint, assessed immediately after the procedure. The primary analytical component of this composite endpoint is procedural anxiety, measured using a 10-point Visual Analogue Scale for Anxiety (VAS-A). The main statistical analysis will compare changes in VAS-A scores between the intervention group and the control group.

The additional dimensions of the composite endpoint, patient-reported comfort, satisfaction and procedural tolerability are collected concurrently and are not aggregated into a single score. These dimensions are analysed separately and interpreted jointly with procedural anxiety in order to provide an overall assessment of the patient’s procedural experience.

Secondary outcomes include: (1) procedural pain, assessed using a 10-point Visual Analogue Scale (VAS); (2) physiological parameters, including heart rate and arterial blood pressure; (3) procedural characteristics, such as procedure duration and number of device insertion attempts; (4) qualitative assessment of patients’ perceptions and lived experiences of the procedure, analysed using Van Kaam’s phenomenological method [18].

The aim of this study is to evaluate the effect of an immersive virtual reality intervention on the overall procedural experience of adult oncology patients undergoing PICC and PICC-PORT placement, with patient experience conceived as a primary dimension of quality of care.

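### Section 2.10 names the pooled-variance t-test while arm sizes are left free; Welch's test would keep the interval accurate if the spreads differ, at practically no cost

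*Protocol article*

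**What the plan says.** For between-group analyses, section 2.10 (Data Management Plan and Analysis) specifies "Independent samples Student’s *t*-tests, or non-parametric equivalents when appropriate". It adds: "Statistical significance will be set at a two-sided *p* < 0.05". Pain and physiological outcomes are to be analysed in a similar way. The section does not mention unequal variances.

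The Outcomes and Aim section defines the main comparison: "The main statistical analysis will compare changes in VAS-A scores between the intervention group and the control group".

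On allocation, section 2.5 says: "Participants are randomly assigned to one of the two study arms in a 1:1 allocation ratio". It continues: "Simple randomisation is employed [20], without any a priori constraint on final group size". No stratification is applied.

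The sample-size paragraph in section 2.10 plans on a 1.5-point difference and a single SD of 2.5 for both arms. This gives 44 per group, raised to about 120 in total.

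**The concern.** By name, Student's two-sample test estimates one common variance. With equal arms it tolerates unequal spreads well. With unequal arms it does not: the larger arm dominates the pooled variance. If the smaller arm is the more variable, the standard error comes out too small; in the reverse case it comes out too large. The plan therefore combines an allocation method that does not secure equal arms with the form of the t-test that relies on them.

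Unequal spread is plausible but not established. If patients respond to VR to different degrees, the SD of VAS-A, or of its change from T0, would differ between arms. What is at stake is the accuracy of the reported interval and p-value at the one split that the trial realises. Section 4 (Discussion) says that the sample is large enough for useful estimates of the anxiety component, so interval accuracy matters to the trial's own aim.

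**Working it through.** **Inputs from the protocol.** Total about 120, 1:1 simple randomisation, two-sided 5% level, difference 1.5, SD 2.5.

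**Assumed, because the protocol has no SDs by arm.** SD 2.5 in the more variable arm and 2.5, 2.0, 1.67 or 1.25 in the other (ratios 1, 1.25, 1.5 and 2), with normal data. Only the ratio matters for the error rates.

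**1. The plan's own figure.** n per group = 2 × (1.960 + 0.842)² × 2.5² / 1.5² = 2 × 7.849 × 6.25 / 2.25 = 43.6, so 44. This agrees with section 2.10. The exact t calculation gives 79.5% power at 44 and 80.4% at 45, a trivial difference. The sample size is not in question.

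**2. How uneven the arms may be.** From Binomial(120, 0.5), the central 95% range is 49:71 to 71:49. The probability of 54:66 or worse is 31.5%; of 50:70 or worse, 8.2%; of 49:71 or worse, 5.5%. Each counts both directions.

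**3. Formula and one worked case.** The true variance of the difference in means is s1²/n1 + s2²/n2. Student's test estimates it, on average, by sp² × (1/n1 + 1/n2), where sp² = [(n1 − 1)s1² + (n2 − 1)s2²] / (n1 + n2 − 2).

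- Smaller arm more variable (50 patients with SD 2.5, 70 with SD 1.667). True variance: 6.25/50 + 2.778/70 = 0.1647. sp² = (49 × 6.25 + 69 × 2.778)/118 = 4.220, and 4.220 × 0.03429 = 0.1447. Ratio of standard errors: √(0.1447/0.1647) = 0.937, so the interval is about 6% too narrow. The effective cut-off is 1.980 × 0.937 = 1.856, and P(|t118| > 1.856) = 6.6%.
- Larger arm more variable (70 with SD 2.5, 50 with SD 1.667). True variance: 0.1448; pooled: 4.808 × 0.03429 = 0.1649. Ratio 1.067, so the interval is about 7% too wide. The cut-off is 2.113, which gives 3.7%.

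Under normality the estimate minus the true difference has the same distribution whatever that difference is. These figures are therefore both the interval's non-coverage when VR works and the rejection rate if means are equal but spreads differ.

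**4. All cases by simulation** (2,000,000 normal-data trials per cell; shorter runs can differ by about 0.1 point). Non-coverage of the nominal 95% interval:

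| Split and more variable arm | Ratio 1 | 1.25 | 1.5 | 2 |
|---|---|---|---|---|
| Student, 60:60 | 5.0% | 5.0% | 5.0% | 5.1% |
| Student, 54:66, smaller arm | 5.0% | 5.5% | 6.0% | 6.6% |
| Student, 54:66, larger arm | 5.0% | 4.5% | 4.2% | 3.8% |
| Student, 50:70, smaller arm | 5.0% | 5.9% | 6.6% | 7.7% |
| Student, 50:70, larger arm | 5.0% | 4.2% | 3.7% | 3.1% |
| Welch, every row | 5.0% | 5.0% | 5.0% | 5.0% |

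**5. Averaged over all splits.** Weighting by the binomial probabilities, Student's error is 5.0 to 5.2% over these ratios and Welch's about 5.0%.

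**6. Whole-number scores from 0 to 10.** With equal means of 3 and SDs of 2.5 and 1.67, Student gives 7.1% at 49:71 and 3.6% at 71:49; Welch gives 5.4% and 4.9%. The pattern does not depend on exact normality.

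**7. Power cost with equal SDs of 2.5 and a 1.5-point difference.** At 60:60 both tests have 90.3%. At 49:71 Student has 89.3% and Welch 89.2%.

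**The case against.** A reader might infer that the trial's type I error is inflated because VR pushes scores towards the bottom of a 0 to 10 scale and so narrows the spread in that arm. The protocol does not support this. Lower anxiety in the VR arm is a treatment effect, so the null hypothesis of equal means is then false. If VR does nothing, the two arms share one distribution and Student's test holds 5% at every split. The main comparison is also described as one of changes in VAS-A, and a change score is not bounded at 0. Over the trial's own randomisation the error stays at 5.0 to 5.2%. All of this stands, and it removes the type I error argument.

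Four further points are fair.

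- The SD ratios are assumptions; the protocol plans on one common SD and nowhere says that VR alters the spread.
- The 8% covers both directions, so the more variable arm would be the smaller one, at 50:70 or worse, in only about 4% of trials.
- Section 2.10 also allows a rank-based alternative, so Student's test is not the only one that may be used. That is not a remedy, because rank tests are affected by unequal spread too.
- The variance form of a t-test is often left to a statistical analysis plan, which is not shown here and may already settle it.

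What remains is that the protocol does name a test, and that the interval is read at one known split. An average over splits that are too liberal and too conservative does not make that interval accurate.

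**Conclusion.** This is a small, optional improvement and not an error in the plan. If VR changes the spread of VAS-A or of its change score, the 95% interval and p-value from Student's test will be slightly too narrow or too wide at an uneven split. For SD ratios up to 1.5, non-coverage lies between 4.2 and 6.0% at 54:66 and between 3.7 and 6.6% at 50:70. It reaches 7.7% or 3.1% only at 50:70 with one SD twice the other. With equal spreads there is no departure at all. The conclusion rests on the assumed ratios and on a total of 120. It does not touch the sample size, and nothing shows that it would alter the trial's conclusion.

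**What to change.** In section 2.10, name Welch's (unequal-variance) t-test in place of Student's for all between-group comparisons of means, and report the matching 95% confidence interval. Nothing else in the design need change.

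The cost is one word in the protocol and at most 0.1 percentage point of power when the SDs are equal. Making the change before the data are seen also avoids a later choice between pooled and unpooled tests guided by the observed SDs. If a statistical analysis plan already names Welch's test, aligning section 2.10 with it is enough.
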